### Control group

As a crossover study, each subject will be his/her own control. This choice is supported by studies that evaluated motor cortical excitability with transcranial magnetic stimulation (TMS) and found that a single tDCS session is able to modify cortical excitability for up to 1.5 hours after the end of stimulation. This suggests that a carryover effect is not an issue [22, 23]. Furthermore, EEG data is one of our outcome measures, and individual characteristics are crucial in this analysis [24], being minimized by a crossover design.

### Outcomes

The primary outcome of this study will be the extent to which this method will change baseline pain intensity (VAS). The subjects will record their experience on a daily basis in a pain diary. A weekly response average will be calculated before the first intervention and after each session. The averages will be used to compare the VAS values before and after each intervention. A decrease of 50 % will be considered a satisfactory clinical improvement.

Secondary outcomes will be the degree of change from baseline in power density of alpha and theta EEG bands. Other outcome measures will be pain pressure threshold (PPT), mechanical pain thresholds (MPTs), and STAI. Increase in PPT and mechanical thresholds indicate an improvement in subject pain condition; a decrease in STAI indicates a better emotional state.

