### Sample size

Following IMMPACT (Initiative on Methods, Measurement, and Pain Assessment in Clinical Trial) [25] recommendations for clinical trials involving chronic pain, we considered our primary outcome measure to be pain intensity changes, assessed through a VAS. We achieved a sample size of 15 subjects (G*Power 3.1), considering a reduction of 50 % (effect size of 0.5), a study power of 80 %, an alpha value of 5 % (*P* < 0.05), and six measures (three pre- and post-measures) on three intervention groups (placebo, and tDCS 1 mA and 2 mA).

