### Data collection procedure

After COAT institutional authorization, subjects will be contacted by phone to ascertain their interest. All interested participants will complete a pre-screening questionnaire. Each subject will be scheduled for an appointment in order to further determine if they meet the inclusion criteria. If they do, they will sign an informed consent and be formerly enrolled in the study.

Women of childbearing age will be required to take a urine pregnancy test during the screening process. If a subject becomes pregnant during the course of the study, she will be withdrawn. During this initial appointment, the subject will be asked to complete a daily pain VAS diary for 7 days. The average VAS score from this data will be used as a baseline pain value.

During a second visit (T2) all clinical and neurological assessments will be performed before and after the tDCS stimulation. The clinical assessments will be measured by VAS pain scores, anxiety measures, and quantitative sensory tests. Neurophysiological assessment will be measured by using an EEG to analyze cortical activity. Each patient will be clinically and neurologically assessed before and after the treatment session resulting in six data collection points (T2 to T7).

All subjects will be treated during a single session for three different interventions (IA, IB,or IC) with a washout period of 7 days between treatments in order to avoid any residual effects. As reported earlier, a single tDCS session usually is able to modify cortical excitability for 1 hour after stimulation [22, 23].

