#### Visual analog scale (VAS) for pain

The VAS allows us to convert subjective sensations, such as pain, into numerical data. A 10-cm scale, where 0 cm is no pain and 10 cm is the worst imaginable pain, will be used, and the subjects will be asked to mark a point on the scale representing their pain intensity. This instrument will be completed everyday in the 7-day period after their acceptance. An average pain intensity score will be calculated as a baseline for the first treatment intervention. Averages for each week will be used to analyze if there will be any treatment carryover effect. The VAS scores will be recorded before and after each treatment session to verify treatment effect.

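### The primary pain outcome is specified inconsistently (weekly diary average or in-session VAS), and the diary version sits badly with the short-effect argument used to dismiss carryover

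*Protocol article*

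**What the plan says.** Two kinds of pain VAS are collected, and Table 1 lists them on separate rows: a daily diary, and a reading before and after stimulation at each of the three sessions.

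- **Outcomes** makes change in VAS pain primary and defines it through the diary. "A weekly response average will be calculated before the first intervention and after each session", and then "The averages will be used to compare the VAS values before and after each intervention". A 50 % decrease counts as satisfactory improvement.
- **Visual analog scale (VAS) for pain** divides the work differently. "Averages for each week will be used to analyze if there will be any treatment carryover effect", whereas "The VAS scores will be recorded before and after each treatment session to verify treatment effect".
- **Data collection procedure** describes assessment "before and after the treatment session resulting in six data collection points (T2 to T7"), and sets a 7-day washout.
- **Sample size** takes pain VAS as primary and uses "six measures (three pre- and post-measures) on three intervention groups", without saying which VAS is meant.
- **Control group** argues against carryover because "a single tDCS session is able to modify cortical excitability for up to 1.5 hours after the end of stimulation". Data collection procedure repeats the argument with a figure of 1 hour.
- **Statistical methods** does not say which VAS is the primary endpoint.

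**The concern.** The section that defines the primary outcome points to one measurement. The section that describes the instrument points to another as the evidence of treatment effect, and the sample size appears to follow the second. A reader cannot tell which result decides the trial. With 15 subjects the two could easily disagree, and either could be reported as primary.

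The two measures also answer different questions. In-session change measures immediate relief. The diary mean measures relief over the following week from a single 20-minute session. If the effect is as short as the carryover argument implies, the week-long mean will contain little of it, and the trial could miss a real immediate effect on the measure that Outcomes calls primary.

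**Working it through.** **1. Counting the measures**

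| Source | Values per subject | Fits six pre/post measures? |
|---|---|---|
| Diary averages (Outcomes) | 1 before the first session + 3 after sessions = 4 | Only by using some averages twice |
| Session VAS (T2 to T7) | 3 sessions × 2 = 6 | Yes |

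Three before/after diary pairs can be formed from the four averages. The before average for sessions 2 and 3 is then the after average of the preceding treatment.

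**2. The stated sample size**

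This used repeated-measures ANOVA power from the noncentral F, with effect size 0.5 read as Cohen's f, alpha 5 %, three groups, and N in multiples of three. For the group-by-time interaction, noncentrality = f² × N × m / (1 − ρ), where m is the number of measures and ρ the correlation between them.

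- m = 2 (pre, post), ρ = 0.5: smallest N = 15, power 87 %.
- m = 6, ρ = 0: smallest N = 15, power 88 %.
- m = 6, ρ = 0.5: N = 9 for the within or interaction test, 27 for the between test.

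So 15 can be reproduced, but only by choosing a test and a correlation that the article does not state. The figure does not settle which VAS was intended.

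**3. How much of a brief effect reaches the weekly mean**

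Inputs: duration 1 to 1.5 h (Control group; Data collection procedure); week = 168 h; one diary mark a day (Outcomes); VAS 4 is the eligibility floor; VAS 7 is an illustrative higher baseline. Assumption: pain relief lasts no longer than the excitability change.

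- Share of the week: 1.5 / 168 = 0.9 %.
- If one of the seven marks falls in the window, baseline B and relief r give a fall in the mean of B × r / 7.
  - Half relief: 0.5 / 7 = 7.1 %, which is 0.5 × 4 / 7 = 0.29 cm at VAS 4 and 0.5 × 7 / 7 = 0.5 cm at VAS 7.
  - Complete relief: 1 / 7 = 14.3 %, which is 7 / 7 = 1.0 cm at VAS 7.
- If no mark falls in the window, the expected shift is zero.

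**4. Power of the diary mean, n = 15**

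This is a two-sided paired t-test at 5 %, noncentrality = (shift / SD) × √15, with one mark inside the window. The SD of within-patient differences in weekly means is an assumption; the documents give none.

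| Shift | SD 0.75 cm | SD 1.0 cm | SD 1.5 cm |
|---|---|---|---|
| 0.29 cm (half relief, VAS 4) | 29 % | 18 % | 11 % |
| 0.5 cm (half relief, VAS 7) | 67 % | 44 % | 23 % |

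Complete relief at VAS 7 (1.0 cm) would give 95 % at SD 1.0 cm, but would still be only a 14.3 % fall.

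**5. What a 50 % fall would require**

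Complete relief for 3.5 of 7 days followed by full return halves the mean: 3.5 / 7 = 50 %. An effect of that length is incompatible with a 1 to 1.5 h rationale, yet it would be over before the next session.

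**The case against.** The strongest reply is that Outcomes is the section that defines the primary outcome, and it names the diary. The VAS section describes an instrument: it neither labels the session reading primary nor restricts the averages to the carryover check, and one data series can serve two purposes. That is fair as far as it goes, and it makes this an ambiguity rather than two rival declarations. It does not remove the problem, because the VAS section still says that the session readings establish the treatment effect and the sample-size count fits them better. That the sample size rests on session VAS remains the likelier reading, not a stated fact.

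A second reply is that the 1 to 1.5 h figure concerns cortical excitability in magnetic-stimulation studies, not analgesia. This stands. The protocol itself, however, carries the figure over to its outcomes when it concludes that carryover is not a concern.

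Three stronger readings are tempting, and the documents do not support them:

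- *The diary mean cannot detect any effect, or is almost certain to be null.* Power is low at the VAS 4 floor, but reaches 67 % for half relief at VAS 7 with the smallest assumed SD, and is higher still for complete relief, provided that a mark falls in the window.
- *The protocol says that pain relief lasts 1 to 1.5 h.* It gives no duration for analgesia.
- *A 50 % fall in the weekly mean would prove carryover.* Step 5 shows that it would not.

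Finally, a sponsor studying pain of at least 6 months' standing could reasonably prefer a diary measure. That choice is open, but it would need a justified window and its own sample size.

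**Conclusion.** The inconsistency is established from the text alone: Outcomes, the VAS section and Sample size do not identify one primary pain measure, so following the plan yields two candidate primary results. This needs correcting because it determines the trial's main conclusion.

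The mismatch between the diary mean and the carryover rationale is conditional. If relief is as brief as the excitability change and there is one mark a day, the weekly mean can fall by at most about 7 % (half relief) or 14 % (complete relief), far below the 50 % criterion. For half relief, with one mark in the window and the assumed SD range, power is 11 % to 67 %, below the planned 80 %. If relief instead lasts for days, the diary could register it, but the short-duration argument against carryover would no longer apply. Whether carryover then occurred at day 7 would be a separate question.

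**What to change.** Before unblinding, by documented amendment and registry update, name one primary pain measure and time point. The choice that best fits Control group, Sample size, Data collection procedure and the VAS section is in-session VAS change (post minus pre), active versus sham. Make the weekly diary mean secondary, for persistence and the carryover check. State which measure the 50 % criterion applies to, and align Outcomes, Sample size and the VAS section.

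If the sponsor keeps the diary mean as primary, it should justify the 7-day window against the durations in Control group and Data collection procedure, and redo the sample size for that measure.

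Cost: an amendment and a registry update, with no new data, since both measures are already collected. Recruitment is under way, so the timing and reason of the change should be recorded. The downside of the first option is a narrower claim: immediate rather than week-long pain relief.

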## Aims

The main objective of this study is to investigate whether cathodal tDCS over the right DLPFC has analgesic effects in subjects with muscular TMD pain. This study will: (1) evaluate the tDCS effect on pain perception and pressure threshold; (2) evaluate whether tDCS has any effect on modifying anxiety and stress; (3) evaluate whether an EEG’s waves change from pre- to post-tDCS; (4) investigate whether there is an association of pain intensity with anxiety and EEG data pre- and post-tDCS; (5) compare the effects of 1 mA and 2 mA over pain intensity, anxiety, stress, and EEG.

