**Fig. 1 Fig1:**
[figure not shown]
Flow of study procedures

**Table 1 Tab1:** Visit summary

	V1	V2	V3	V4
	Baseline/consent	1^st^ session	2^nd^ session	3^rd^ session
Consent form	X			
RDC/TMD	X			
VAS pain diary	X	X	X	X
VAS pain (pre-tDCS)		X	X	X
Sensory testing (pre-tDCS)		X	X	X
EEG recording (pre-tDCS)		X	X	X
tDCS stimulation (IA, IB, or IC)		X	X	X
Adverse effects questionnaire		X	X	X
VAS pain (post-tDCS)		X	X	X
ISTA	X	X	X	X
EEG recording (post-tDCS)		X	X	X
Sensory testing (post-tDCS)		X	X	X
*Approx. time*	*1 hour*	*3 hours*	*3 hours*	*3 hours*

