#### Electroencephalogram (EEG)

The EEG is a powerful tool to assess changes related to anxiety [29]. It will measure the brain’s electrical current intensity, using the analysis of alpha and theta waves. Alpha waves are related to physical relaxation and are higher when the subject keeps his/her eyes closed. Alpha power density is reduced when the eyes are open. The same can be seen in relaxation and alertness respectively. Theta waves are related to awareness states and are higher chronic pain conditions.

For this study, a 32-channel EEG (BrainNet BNT 36, EMSA, Brazil) will be used. Data will be band pass filtered (0.5 to 50 Hz) and acquired at 200 Hz. The channel location will be used according to the International 10–20 EEG System. Wave power and frequency will be checked before and after tDCS stimulation. The reference electrodes will be located at Cz. The data will be analyzed in MATLAB (The Mathworks, Inc., Natick, MA, USA). After signal filtering, data will be epoched into 1.28-second segments to standardize artifact removal. Artifacts will be removed using EEGLab (the semi-automated rejection EEGLab). Epochs containing extreme values (above −750 and below 750 μV) will be rejected using independent component analysis (ICA), removing the first component. After artifact removal, a frequency analysis will be run based on the following band widths: a) theta (4–8 Hz), b) alpha (8–12 Hz), and c) beta (13–30Hz).

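### EEG secondary outcome: the baseline is loosely named, and the planned pre/post ANOVA uses the same-session pre-tDCS recording less efficiently than covariate adjustment would

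*Protocol article*

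**What the plan says.** Under Outcomes, the protocol article defines the EEG endpoint thus: "Secondary outcomes will be the degree of change from baseline in power density of alpha and theta EEG bands". It does not identify the baseline recording.

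Other sections describe the EEG comparison as before against after stimulation. The third aim is to "evaluate whether an EEG’s waves change from pre- to post-tDCS". The EEG section says: "Wave power and frequency will be checked before and after tDCS stimulation". Data collection procedure places an assessment before and after each of the three sessions, which makes six collection points. Statistical methods plans repeated-measures analysis of variance on pre- and post-intervention values, between and within interventions, with nonparametric tests as the alternative.

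The one baseline value that Data collection procedure defines is for pain, from the 7-day diary: "The average VAS score from this data will be used as a baseline pain value". Table 1 labels the first visit "Baseline/consent" and schedules no EEG there. EEG is recorded before and after tDCS at visits 2, 3 and 4.

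**The concern.** Two things follow from how the EEG outcome is written.

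First, the word used in the outcome definition is not tied to a recording. It is defined explicitly only for the pain diary, and the visit that carries the label has no EEG. The reader has to infer the meaning from other sections.

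Second, once that inference is made, the named analysis does not make the best use of the data. Each patient has a pre-tDCS EEG at every session. The repeated-measures ANOVA uses it by subtraction, which in effect fixes the slope of post on pre at 1. If the true within-patient slope is below 1, subtraction adds noise from the pre recording to the treatment contrast. With 15 patients, that can matter for the only outcome the article names as secondary.

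**Working it through.** **Plan's own figure.** There is none for EEG. The 15 subjects under Sample size were derived for VAS pain, and the article gives no EEG effect size, SD, correlation or power. The number 15 is taken as given here.

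**Inputs from the article:** 15 patients, three sessions each, three conditions (1 mA, 2 mA, sham), one pre and one post EEG per session, alpha 5 %.

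**Assumptions:** two-sided test (sidedness is not stated); three balanced orders; a true active-minus-sham difference of 0.8 within-patient SD; equal within-patient SD before and after (set to 1); no carryover; ρ = 0.2, 0.5 and 0.8, where ρ is the within-patient correlation of pre and post in the same session.

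This ρ is net of stable patient differences. If ρ_w is the ordinary pre/post correlation within a session and ρ_b the correlation between sessions, ρ = (ρ_w − ρ_b)/(1 − ρ_b). For example, ρ_w = 0.9 with ρ_b = 0.5 gives 0.4/0.5 = 0.8, and ρ_w = 0.6 with ρ_b = 0.5 gives 0.1/0.5 = 0.2.

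**Step 1: residual variance.**
- Change score: Var(post − pre) = 1 + 1 − 2ρ = 2(1 − ρ).
- Post adjusted for same-session pre: 1 − ρ².
- Difference: 2(1 − ρ) − (1 − ρ²) = (1 − ρ)², which is never negative.
- Ratio, adjusted to change: (1 + ρ)/2, that is 0.60, 0.75 and 0.90 for the three values of ρ.

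**Step 2: standard error of a treatment contrast.** With patient, period and treatment terms in a balanced layout, SE = √(2/15 × residual variance).
- ρ = 0.2: change √(0.1333 × 1.60) = 0.46; adjusted √(0.1333 × 0.96) = 0.36.
- ρ = 0.5: change √(0.1333 × 1.00) = 0.365; adjusted √(0.1333 × 0.75) = 0.32.
- ρ = 0.8: change √(0.1333 × 0.40) = 0.23; adjusted √(0.1333 × 0.36) = 0.22.

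**Step 3: residual degrees of freedom.** There are 45 session records. Change score: 45 − 15 (patients) − 2 (periods) − 2 (treatments) = 26. The covariate takes one more and leaves 25.

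**Step 4: power for a difference of 0.8.**

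| ρ | Change score, simulated | Adjusted, simulated | Change score, noncentral t | Adjusted, noncentral t |
|---|---|---|---|---|
| 0.2 | 37 % | 55 % | 39 % | 58 % |
| 0.5 | 55 % | 65 % | 56 % | 68 % |
| 0.8 | 91 % | 92 % | 92 % | 94 % |

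The noncentral t figures for the adjusted analysis are slightly high because they ignore the estimation of the covariate slope. The simulated figures include it and are the ones to use.

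**Step 5: in patients.** Dividing 15 by the variance ratio gives the number that a change-score analysis would need for the same standard error: 15/0.60 = 25, 15/0.75 = 20 and 15/0.90 = about 17.

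**The case against.** **Is the plan self-contradictory?** A reader might infer two rival definitions: change from one fixed pre-treatment value, and change within each session. The documents do not support that. With no EEG at the first visit, a change from that visit cannot be computed, which removes the reading. A common baseline taken from the first pre-tDCS recording is stated nowhere. It would leave the pre recordings of the second and third sessions unused and would depart from the stated pre/post analysis. Aims, Data collection procedure, the EEG section and Statistical methods all point to the same session. It follows that a power gap between those two readings is not a property of this plan.

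**Are the sensory tests affected?** A reader might extend the wording problem to pressure and mechanical pain thresholds. They are listed in a separate sentence that does not mention baseline, so their absence from the first visit conflicts with nothing.

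**Is this detail for an analysis plan?** Covariates and model terms are often left to one, and one may exist. That stands as to completeness. But the article does name a method, and that method leads to the change score, so recommending a more efficient use of scheduled data is fair.

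**Are the figures real?** They are illustrative. Effect and correlation are assumed, and at ρ = 0.8 the gain is about one point. The variance inequality itself does not depend on these values.

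**Could the analysis be chosen to suit the data?** The biostatistician is blinded and the randomization list is to stay closed until the data have been analyzed, so this worry is largely met.

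**Conclusion.** The concern holds as an efficiency point with a small wording correction attached. The EEG baseline is not identified where the outcome is defined, although the rest of the article makes the intention clear. Under equal pre and post variances, the planned ANOVA contrast has residual variance 2(1 − ρ) against 1 − ρ² after adjustment, so adjustment never gives a larger residual variance. Under the assumed difference of 0.8 within-patient SD, the gain in simulated power is about 18 points at ρ = 0.2 (37 to 55 %), 10 at ρ = 0.5 (55 to 65 %) and 1 at ρ = 0.8 (91 to 92 %). The actual gain in this trial cannot be known from the documents, because they give no EEG effect size, SD or correlation. The planned analysis is not invalid. It may be less precise than the scheduled data allow.

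**What to change.** - **Outcomes:** state that, for EEG power density, baseline means the pre-tDCS recording of the same session.
- **Statistical methods:** for alpha and theta power, analyze the post-tDCS value as the response, with the same-session pre-tDCS value as covariate and patient, period and treatment as terms. Report the contrasts of 1 mA and 2 mA with sham and with each other.
- **Optional:** use the same model for the pressure and mechanical pain thresholds, which are also measured before and after tDCS at every session. This is for consistency and precision, not to cure a wording fault.

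Cost: a sentence or two in two sections and one residual degree of freedom (25 instead of 26). No visit, recording or patient is added. When ρ is high, the gain is close to nil, but so is the loss.

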### Participant timeline

All study procedures are depicted in Fig. 1, and the visit summary is given in Table 1.

**Fig. 1 Fig1:**
[figure not shown]
Flow of study procedures

**Table 1 Tab1:** Visit summary

	V1	V2	V3	V4
	Baseline/consent	1^st^ session	2^nd^ session	3^rd^ session
Consent form	X			
RDC/TMD	X			
VAS pain diary	X	X	X	X
VAS pain (pre-tDCS)		X	X	X
Sensory testing (pre-tDCS)		X	X	X
EEG recording (pre-tDCS)		X	X	X
tDCS stimulation (IA, IB, or IC)		X	X	X
Adverse effects questionnaire		X	X	X
VAS pain (post-tDCS)		X	X	X
ISTA	X	X	X	X
EEG recording (post-tDCS)		X	X	X
Sensory testing (post-tDCS)		X	X	X
*Approx. time*	*1 hour*	*3 hours*	*3 hours*	*3 hours*

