An advantage of tDCS is that it has minimal side effects. The most common adverse effects are itching, tingling, and mild headache that resolve just after the stimuli is terminated. These adverse effects depend on the intensity and duration of the treatment session. The most common protocols use a lower intensity (1 or 2 mA) with a treatment session duration of 20 or 30 minutes. To access tolerability and safety of tDCS, a side effect questionnaire has been developed [19].

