### Intervention C

This will be the sham intervention. Stimulation electrodes will be placed at the same areas as for interventions A and B, but the current will be applied only for the first 30 seconds, after which it will be reduced gradually until it reaches zero. This method has been shown to be effective in previous studies [21].

In all the intervention groups, tDCS will be applied using 35 cm^2^ (5×7 cm) sponge electrodes soaked in saline solution (140mMolNaCl, water dissolved in Mille-Q). Anodal and cathodal electrodes will be connected in the tDCSdevice (Soterix Medical 1 × 1 tDCS 1300A, USA). Two 9-V batteries will deliver current.

All subjects will receive only one stimulation session for each type of intervention (IA, IB and IC), for a total of three sessions. After each tDCS session, the subject will complete a questionnaire to record any adverse affects. A trained researcher ([name]) will perform each procedure. One researcher who is responsible for the general supervision ([name]) during testing will hold the randomization list, and only the clinician responsible for the tDCS stimulation will know which intervention group is being applied. All clinical and neurological assessments will be performed at the Functional Electrostimulation Laboratory at Federal University of Bahia (Salvador, Brazil).

As this is a crossover study with only four weekly sessions, we believe that there will not be a compliance problem. Furthermore, since side effects are minimal, there is a low risk of dropouts due to this reason.

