### Safety monitoring

At each stimulation session, subjects will complete a questionnaire to evaluate potential adverse effects of tDCS (tingling, burning sensation, headache, neck pain, mood alterations) on a 5-point scale. Subjects will be asked whether they experienced any side effects in an open-ended manner, and they will be specifically asked about headache, neck pain, scalp pain, burning sensations, tingling, skin redness, sleepiness, trouble concentrating, and acute mood change.

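### Table 1 lists the itemised adverse-effects questionnaire before the post-stimulation pain rating, which can weaken the patient blind; state the within-visit order and move the form to the end

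*Protocol article*

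**What the plan says.** Table 1 (Participant timeline) gives these rows for each of the three stimulation visits: pre-stimulation VAS, sensory testing and EEG; stimulation; "Adverse effects questionnaire"; "VAS pain (post-tDCS"); the anxiety inventory (printed as ISTA, one row, not labelled pre or post); post-stimulation EEG; post-stimulation sensory testing.

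The text mentions the timing of the questionnaire twice. Under Intervention C: "After each tDCS session, the subject will complete a questionnaire to record any adverse affects". Under Safety monitoring: "At each stimulation session, subjects will complete a questionnaire to evaluate potential adverse effects of tDCS". Neither sentence places it relative to the post-stimulation outcomes.

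On content, Safety monitoring has an open question and a prompted list: "they will be specifically asked about headache, neck pain, scalp pain, burning sensations, tingling, skin redness, sleepiness, trouble concentrating, and acute mood change". On what the answers depend on, the Background says: "These adverse effects depend on the intensity and duration of the treatment session". Under sham, "the current will be applied only for the first 30 seconds, after which it will be reduced gradually until it reaches zero"; the two active interventions run for 20 minutes. Each patient has one session of each.

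The section on the VAS says that the ratings around each session serve to show whether the treatment worked. The Outcomes section defines the primary outcome on weekly averages of a daily diary.

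**The concern.** The session VAS and the STAI are self-reported, and only the sham procedure protects them from expectation. A prompted, scored list of stimulation sensations asks the patient to take stock of how strong the current felt. In a crossover, the patient can set that against earlier sessions. If the next thing the patient does is rate pain, a belief about which condition was given can enter the rating. Several items (head, neck and scalp pain, mood) also overlap in content with pain and state anxiety.

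The contrasts at stake are active against sham and 1 mA against 2 mA on session pain and, if the order holds for it, on anxiety. These belong to the main objective and to aims 2 and 5.

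**Working it through.** The protocol gives no figure on this point, so none can be reproduced. The check is a comparison of passages with a few counts.

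1. **Is Table 1 a running order?** The rows go from pre-stimulation tests through stimulation to post-stimulation tests, under a heading about the timeline. Sensory testing precedes EEG in the pre block and follows it in the post block; a plain checklist would have little reason to reverse them. This suggests chronology but does not prove it. The table is called only a visit summary, and the flow chart (Fig. 1) is not available.

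2. **Does the text correct the order?** No. Both sentences on timing fit a form completed straight after stimulation and equally a form completed at the end of the visit.

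3. **Do the answers carry information on the condition?** By the protocol's own statement, yes, since the effects vary with intensity and duration. Active stimulation lasts 20 × 60 = 1,200 s. Sham current is held for 30 s before an unspecified ramp-down. 1,200 / 30 = 40, so the time under current differs by a factor of about 40 before the ramp is counted.

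4. **How many sessions allow a comparison?** 15 patients × 3 sessions = 45. Sessions with at least one earlier session: 15 × 2 = 30. The 15 first sessions offer nothing to compare with.

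5. **Which part would fail to cancel?** Write a post-stimulation rating under condition c as

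   rating = true value + a + s(c) + q(c),

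   where a is the effect of filling in the same list every time, s(c) the expectation from sensations felt whether or not anyone asks, and q(c) the extra effect of scoring them just beforehand. For active minus sham, a drops out and the bias is [s(active) − s(sham)] + [q(active) − q(sham)]. Only the second bracket is due to where the form stands. The documents give no value for it.

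6. **Which outcomes are exposed?**
   - Session VAS: yes, on the listed order.
   - STAI: uncertain. The Data collection section puts anxiety measures both before and after stimulation, while the table has one unlabelled row.
   - Weekly diary average: not directly, because it is recorded day by day and not just after the form.
   - The session VAS is not peripheral, however. The Sample size section counts six measures, three pre and three post. That fits the six session time points (T2 to T7) and not the 1 + 3 = 4 weekly averages described under Outcomes.

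**The case against.** The strongest reply is that row order is being read as clock order. No sentence says that the rows are chronological. The diary, which is kept daily, also appears as a visit row, and read strictly the table would leave no pre-stimulation STAI on treatment days, against the Data collection section. A condensed article may leave within-visit order to the full protocol. This stands as a limit on certainty. It does not remove the point, because the only order visible in the article puts the form first.

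Second, patients feel the current whether or not they are asked, sham also delivers current, and the Intervention C section calls this sham method effective. This stands: the questionnaire can heighten a contrast already felt, and no more. A reader might infer that it reveals the allocation or breaks the blind; the documents do not support that.

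Third, prompt recording has value, since the Background says that the common effects fade once the current stops. This is the real cost of moving the form. The same fact cuts the other way: the list brings fading sensations back to attention just before pain is rated.

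Fourth, from session 2 the patient knows the list, so moving it cannot prevent all comparison. That is true; it removes only the immediate prompt.

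Fifth, the documents do not say that outcome assessors see the answers. Cueing of the assessor is a possibility to close off and not an established fault.

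**Conclusion.** The point holds as a modest design weakness. As listed, a prompted sensation form comes before the self-rated session VAS, and possibly the STAI, and the text does not place it later. By the protocol's own account the answers vary with the stimulation given, so the part of the effect that depends on condition need not cancel against sham. This rests on reading Table 1 as a running order, which is likely but not certain. If it is not one, the order is open in the article and should be stated.

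The size is unknown. A reader might try to scale it: an assumed shift of 0.5 or 1 cm would be 0.5/2 = 25 % or 1/2 = 50 % of the 2 cm that a 50 % fall means at the entry score of 4. Those shifts have no source in the protocol, and the 50 % criterion is attached to the weekly averages, so the percentages say nothing about the likely bias. A reader might also infer that the primary outcome is biased; as defined under Outcomes, it is not directly exposed.

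**What to change.** State the within-visit order in the protocol, label the STAI row as pre, post or both, and move the adverse-effects questionnaire after the post-stimulation VAS, STAI, EEG and sensory testing. Leave spontaneous reports and safety observation during stimulation as they are. Keep the completed form from whoever does the post-stimulation tests.

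If the investigators want to test the blind with a treatment-guess question, ask it only once, after the last outcome, including the final diary week, has been collected. Asked at every session, it would itself prompt guessing before later sessions and before the next week's diary.

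The cost is one row moved and one or two sentences added. Brief sensations would be recalled somewhat later, within the same three-hour visit.
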